## Methods

### Study objectives

The goals of the TOEC-Eastern Africa study are:To describe the treatment patterns for ESCC at referral hospitals in Eastern Africa.To investigate the outcomes of different ESCC treatments in Eastern Africa, specifically overall survival, QOL, and safety, with a particular focus on palliative interventions including chemotherapy, radiotherapy with or without chemotherapy, esophageal stenting with SEMS, and supportive care.To examine process measures related to the delivery of ESCC treatment at referral hospitals in Eastern Africa, including time from presentation to initiation of treatment, total time to deliver an intervention, and total number of days hospitalized during and after ESCC treatment.To assess utilization of healthcare resources by ESCC treatment approach, as measured by hospitalization events (total number of times hospitalized and cumulative days hospitalized) and need for subsequent intervention for recurrent or persistent dysphagia.

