#### Exploratory endpoints

Exploratory endpoints related to processes of care will also be measured, including time from presentation to initiation of ESCC treatment, time to deliver intervention (defined as total time elapsed from initiation of treatment to last day of treatment), and total number of days hospitalized during and after an intervention. Measures of healthcare utilization that will be assessed include hospitalization events (total number of times hospitalized and cumulative days hospitalized), and the proportion of patients receiving a subsequent intervention for recurrent or persistent dysphagia. Hospitalization is defined as admittance to the inpatient setting of a hospital (medical or surgical ward or intensive care unit) for a period of ≥24 h per participant report.

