### Recruitment and consent of study participants

Patients who present to participating AfrECC sites with symptoms concerning for or a new diagnosis of EC will be identified by the research team. Since many patients with ESCC are ill and subject to clinical deterioration, we will employ rapid case ascertainment strategies to identify all cases of EC seen for further care. Study teams are embedded in clinical care settings. At designated times each week, research coordinators will use the following strategies to identify eligible patients with suspected diagnoses of ESCC: 1) contact physicians caring for inpatients on both medical and surgical wards and review current ward rosters; 2) review the schedule of endoscopy cases to be performed, including diagnostic and therapeutic procedures (if applicable); 3) review pathology reports (if applicable); 4) contact clinicians seeing patients in the outpatient setting; and 5) review chemotherapy and radiation schedules to identify patients with plans to undergo ESCC treatment (if applicable).

Once potential study participants are identified, they will be approached by a research assistant to assess eligibility and willingness to participate in this study. Study participants will be thoroughly informed about all aspects of the study, including study follow up plans and all regulatory requirements for informed consent. Written informed consent will be obtained prior to study enrollment. The informed consent documents will be available in both English and the local language(s) at each site. Study participants will receive a phone card as a small token of compensation for participation, valued at 5 USD in Kenya and Tanzania and 10 USD in Malawi, in accordance with the local institutional standards.

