### Data collection procedures

#### Case report forms (CRFs)

CRFs are comprised of both medical chart abstraction instruments and standardized questionnaires. CRFs collect socio-demographic details (including age, sex, ethnicity, location of permanent residence, highest level of education completed, self-reported annual household income, health insurance status), baseline clinical information, treatment-related data, as well as vital status and QOL metrics over long-term follow up (see Table 3).

**Table 3 Tab3:** Data collected during TOEC-Eastern Africa study

Collected data	Baseline	Prior to treatment	During treatment	Follow up^**a**^
Sociodemographic				
Age	x			
Sex	x			
Ethnicity	x			
Occupation	x			
Location of permanent residence	x			
Highest level of education completed	x			
Annual household income	x			
Health insurance status	x			
Smoking and alcohol use	x			
Clinical data				
Medical History	x			
HIV status (date of and last CD4 count, use of antiretrovirals)	x			
Date/method of diagnosis	x			
Histopathological data (if applicable)	x			
Endoscopic findings (location/length of tumor)	x			
Imaging (if applicable)^b^	x			
Use of opiate medications for pain control	x	x		x
Hospitalizations			x	x
Vital status (including cause of death, if applicable)			x	x
Treatment				
Prior EC treatment (if applicable)	x			
EC treatment received, including delays/interruptions in treatment and reasons			x	
Complications			x	
Response assessment (if applicable)			x	
Quality of life				
Modified Rosenblatt Index^c^	x	x		x

*EC* Esophageal cancer

^a^Follow up assessments performed 1 month after initiation of treatment, 3 months after initiation of treatment, and then every 3 months until death or loss to follow up

^b^Any imaging modality performed during baseline assessment, including chest x-ray, ultrasound, computed tomography, positron emissions tomography, etc.

^c^The Modified Rosenblatt Index assesses the following: Dysphagia, Odynophagia, ‘Chest and/or Back pain,’ WHO performance status, and ‘Overall Well-being’ since starting treatment

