### Statistical methods

All patients consenting to study participation with a histopathologically-confirmed or clinical diagnosis of EC will be included in the analyses. Descriptive statistics will be used to describe the proportion of ESCC patients receiving treatment with each modality at participating AfrECC sites. We will assess the associations between demographic/clinicopathologic characteristics and the treatment modalities employed (chemotherapy, radiotherapy, chemoradiation, esophageal stenting with SEMS, esophagectomy, supportive care alone). Categorical variables and continuous variables will be compared among the groups using Pearson’s Chi-squared test, and Analysis of Variance (ANOVA) (or Kruskal Wallis test when normality assumption is not held), respectively. Possible transformation (e.g., logarithm transformation) will be performed if the data is skewed.

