OS will be defined in two ways: 1) from the date of initial diagnosis to the date of death or last patient contact; and 2) from date of initiation of treatment to date of death or the date of last patient contact. Kaplan-Meier method will be used to summarize OS and log-rank test will be used to compare survival curves among treatments overall and stratified by the study center. Furthermore, Cox proportional hazards (cph) modeling will be used to account for demographic and clinicopathological factors by including them as covariates. Proportionality of hazards for key covariates will be tested by examining the correlation between time and scaled Schoenfeld residuals and log-log plots of survival. Important covariates that violate the proportionality assumption will be used to stratify the cph model. In many settings in Eastern Africa, long delays can occur between diagnosis and initiation of treatment. To mitigate immortal time bias that can emerge in time-to-event analyses of observational studies, two analytical approaches will be employed. First, in analyses using OS defined by date of diagnosis, the time from diagnosis to the initial treatment will be added as a covariate. Secondly, in analyses of associations between different treatments and OS, treatment status will be included in Cox regression modeling as a time-varying covariate (defined as treated versus untreated). This approach allows for patients to accrue follow up time while awaiting treatment, while also accounting for any events that occur during the ‘untreated’ waiting period [20]. Our primary analysis will examine pairwise comparisons of: stenting vs. radiotherapy with or without chemotherapy, stenting vs. chemotherapy, and radiotherapy with or without chemotherapy vs. chemotherapy. Among patients receiving radiation, outcomes may differ between patients receiving radiotherapy alone as compared to concurrent chemoradiation. Exploratory analyses will examine these subgroups separately.

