Cochran-Armitage test will be used to compare symptom metrics assessed using the ‘Modified Rosenblatt Index’ (Dysphagia, Odynophagia, ‘Chest and/or Back pain,’ WHO performance status, and ‘Overall Well-being’ since starting treatment) between each of the different palliative EC treatments (chemotherapy, radiotherapy, chemoradiation, esophageal stenting, basic supportive care) at each time point: 1 month after initiation of treatment, 3 months after the initiation of treatment and then every 3 months thereafter. We will also test for within-subject differences in scores between baseline (or pre-treatment) and each of post-treatment time points by McNemar’s Chi-squared test. In addition, generalized estimating equations (GEE) framework will be applied to analyze this longitudinal QOL data, where the treatment will be considered as the fixed effect and the subject-specific effects are the random effects.

Complications will be summarized as number of patients (%) with 95% confidence intervals and compared between treatment arms by Chi-squared test. Among palliative interventions, secondary outcome measures related to dysphagia will be compared using log-rank test and cph models to adjust covariates, including age, sex and baseline clinical covariates. ‘Time to achieve any dysphagia relief’ will be defined as time from treatment to improvement in dysphagia score of greater than or equal to 1. ‘Duration of dysphagia relief’ will be defined as time elapsed after treatment with any improvement in dysphagia from baseline. ‘Dysphagia-adjusted survival’ will be defined as the total time period with a dysphagia score of 0 to 2.

Measures of healthcare utilization and process measures related to the delivery of ESCC treatment by treatment approach will be examined as exploratory endpoints. Time-to-event measures will be compared among treatment groups by log-rank test. Count of hospitalization events, and total number of days hospitalized during and after ESCC treatment will be compared among treatment groups by ANOVA (or Kruskal Wallis test when normality assumption is not held). Chi-squared test will be used to compare the need for subsequent intervention for recurrent or persistent dysphagia by treatment approach. All analyses will be performed overall and within each site.

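### The exploratory comparison of time from presentation to treatment uses groups defined by treatment received, so it conditions on surviving the wait and leaves out deaths before treatment

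*Protocol article*

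**What the plan says.** The third study objective covers process measures, "including time from presentation to initiation of treatment, total time to deliver an intervention". The Exploratory endpoints section repeats them: "including time from presentation to initiation of ESCC treatment, time to deliver intervention".

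The Statistical methods section examines process measures by treatment approach, as exploratory endpoints, and fixes the test: "Time-to-event measures will be compared among treatment groups by log-rank test".

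The groups are described by what was given. The descriptive analysis reports "the proportion of ESCC patients receiving treatment with each modality at participating AfrECC sites", and Table 3 collects "EC treatment received, including delays/interruptions in treatment and reasons". Neither the text nor Table 3 defines a planned or intended modality.

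The protocol knows that waiting matters: "In many settings in Eastern Africa, long delays can occur between diagnosis and initiation of treatment". In explaining its rapid case finding it also says: "Since many patients with ESCC are ill and subject to clinical deterioration". Statistical methods gives two remedies for waiting time, delay as a covariate and treatment status as a time-varying covariate. Both are stated for overall survival only.

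**The concern.** A patient belongs to the radiotherapy, chemotherapy or stenting group only once that treatment has begun. For most outcomes this is a familiar source of immortal time. Here it is more direct, because the outcome is the start of treatment itself, so group membership already implies that the event has happened. Patients who die or deteriorate before starting are absent from the group whose delay is being measured.

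The third objective asks how care is delivered at these hospitals. If some patients do not live through the wait, a wait measured only in those who do can look shorter than the one patients face, and contrasts between modalities can shrink. The number who die before any treatment, which bears directly on that objective, has no line of its own in the planned results.

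**Working it through.** **1. Which measures the log-rank sentence covers.** Exploratory endpoints lists two durations of this type: time from presentation to initiation, and time to deliver the intervention (first to last day of treatment). The second exists only in treated patients, so restricting it to them is correct. The problem concerns the first.

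**2. Whether the groups leave room for patients who die waiting.** The Sample size section forecasts stenting 1102, chemotherapy 145, radiotherapy 464, chemoradiation 212, supportive care alone 450 and esophagectomy 103:

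1102 + 145 + 464 + 212 + 450 + 103 = 2476.

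This reproduces the planned enrolment exactly. No category remains for a patient headed for a modality who dies before it starts. Such a patient can only fall into supportive care alone or into no group.

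**3. What each group contributes to the log-rank test.** In each active group every patient has the event. In supportive care alone nobody has a start date, so time to initiation is undefined. A death while waiting enters no active group, either as a competing event or as a censored time.

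**4. Size, as an illustration only.** The protocol gives no waiting times and no figure for this measure, so there is nothing of its own to reproduce. Assumed inputs:

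- True median wait w: 4 or 12 weeks (assumption).
- Median survival while waiting d: 14 to 36 weeks. These are the lowest and highest OS medians in Sample size (chemotherapy and stenting). They describe treated patients and serve here only as a proxy.
- Death and waiting times independent; survival exponential.

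With exponential waits, the hazards are ln2/w for starting and ln2/d for dying, so:

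- Share dying before starting = w/(w + d)
- Median wait among those treated = wd/(w + d)

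For w = 4:
- d = 14: 4/18 = 22%; 56/18 = 3.1 weeks
- d = 36: 4/40 = 10%; 144/40 = 3.6 weeks

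For w = 12:
- d = 14: 12/26 = 46%; 168/26 = 6.5 weeks
- d = 36: 12/48 = 25%; 432/48 = 9.0 weeks

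**5. Sensitivity to the shape of the waits.** Lognormal rows come from simulation with 1,000,000 draws. For a wait that is the same for everyone, the share dying is 1 − 2^(−w/d). Ranges span d = 14 to 36 weeks.

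| Waits | True median (weeks) | Die before starting | Median among treated (weeks) |
|---|---|---|---|
| Exponential | 4 | 10-22% | 3.1-3.6 |
| Exponential | 12 | 25-46% | 6.5-9.0 |
| Lognormal, log-SD 0.7 | 4 | 9-21% | 3.6-3.8 |
| Lognormal, log-SD 0.7 | 12 | 24-47% | 9.3-10.7 |
| Same for everyone | 4 | 7-18% | 4.0 |
| Same for everyone | 12 | 21-45% | 12.0 |

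The bias in the median depends strongly on how much waits vary. The unseen share of deaths does not go away under any of the three shapes.

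**6. Effect on a contrast.** Take exponential waits, d = 27 (the protocol's radiotherapy median) and two queues with true medians of 2 and 12 weeks. The observed medians are 54/29 = 1.86 and 324/39 = 8.31 weeks. The true gap of 10 weeks reads as about 6.4. The slower queue still reads as clearly slower.

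**The case against.** The strongest reply has four parts.

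- **The endpoint is exploratory.** This stands. Neither the primary OS comparison nor its stated power changes, and the point should be graded accordingly.
- **The text does not say that only starters enter.** It speaks of treatment groups, includes all consenting patients in the analyses, and chooses a test that normally implies censoring; at-risk rules may sit in a fuller document. It is true that the article does not say how deaths before treatment are classified. But including every patient does not return someone who died waiting to the modality awaited. With no planned modality defined, there is no group in which that patient could be censored. The comparison by group received is stated, not left open.
- **Related information is already planned.** Patients on supportive care alone are counted, reasons for pursuing supportive care are abstracted, and all analyses are also run within each site. A reader might infer that those who never reach treatment go unreported altogether. The documents do not support that; what is missing is a separate figure for those who died before any treatment. Running the same comparison within sites repeats the same conditioning.
- **The wait among treated patients is a legitimate description.** This stands, provided it is labelled as conditional on starting.

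A reader might also infer that radiotherapy would be made to look close to same-day stenting because patients are referred to ORCI. The protocol gives no waiting time for stenting. Referral to ORCI is site-specific: Table 1 shows external beam radiotherapy on site at ORCI and MTRH, gives referral to ORCI for KCMC, and the site description reports referrals from MNH.

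**Conclusion.** The point holds for one exploratory measure. As written, the log-rank comparison of time from presentation to treatment conditions on having started, so it cannot show deaths in the queue, and the protocol's handling of waiting time does not extend to it.

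The size cannot be determined from the document. The illustrative shares of 10-22% dying before a 4-week median wait and 25-46% before a 12-week one rest on assumed waits and on post-treatment survival medians used as a proxy. The matching understatement of the median (to 3.1-3.6 and 6.5-9.0 weeks) also needs exponential waits. It is smaller with lognormal waits and near zero when waits within a queue hardly vary.

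A reader might conclude that delay is necessarily understated most where queues are longest. That requires the spread of waits to grow with their length, which is plausible but not documented. What rises with queue length under every shape tried is the share who die unseen.

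This is a change worth considering; it is no threat to the study's main conclusions.

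**What to change.** For this measure only, replace the log-rank test by treatment received with the following:

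- **Population:** all enrolled patients with no earlier treatment for esophageal cancer.
- **Estimate:** cumulative incidence of starting any treatment, and of starting each modality, from presentation, overall and by site.
- **Events:** death before treatment as a competing event; loss to follow-up as censoring.
- **Entry:** where enrolment follows presentation, patients join the risk set at enrolment (delayed entry), so that the interval before enrolment does not become immortal time in its turn.
- **Report:** the proportion dying before any treatment.

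The wait among treated patients can stay as a description labelled as conditional on starting. Time to deliver the intervention stays restricted to treated patients. An analysis by planned modality is not proposed, because Table 3 lists no such item.

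The cost is slightly more analysis work and reported delays that may look less favourable. Chart abstraction already covers treatment dates and date of death. Two items need confirming. Table 3 lists the date of diagnosis but not of presentation, which the endpoint needs in any case. It also marks vital status only during treatment and at follow-up, with follow-up timed from the start of treatment, so capture of deaths before treatment should be checked. Sample size and the primary OS analysis do not change.

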### Sample size

We aim to recruit all patients with ESCC based on histological confirmation or presumptive clinical diagnosis that meet the eligibility criteria at participating AfrECC sites. We forecast a total accrual of an estimated 2476 study participants across all six sites (see Table 1) over the duration of the study. This estimate is based on annual ESCC cases observed in recent case series at KCH (unpublished data), annual recruitment to a recent case-control study at KCMC [18], as well as annual accrual rates in the present study at ORCI, MNH, and Tenwek since study initiation (Tenwek Hospital, *n* = 220 study participants per year; ORCI, *n* = 130 per year; and MNH, *n* = 150 per year). Of the total study population, we estimate 1102 study participants will be treated with esophageal stenting, 145 with chemotherapy, 464 with radiotherapy, 212 with concurrent chemoradiation, 450 with supportive care alone, and 103 with esophagectomy. Based upon previous data that indicate median OS following stenting is 36 weeks [10], radiotherapy with or without chemotherapy is 27 weeks [13, 19], and chemotherapy is 14 weeks [5, 19], our primary analysis comparing OS of different palliative interventions for ESCC will have the following power to detect differences between each pairwise comparisons based upon alpha of 0.0167 (adjusting for 3 comparisons based on Bonferroni correction): stenting vs. radiotherapy with or without chemotherapy, power = 0.99; stenting vs. chemotherapy, power = 1.00; and radiotherapy with or without chemotherapy vs. chemotherapy, power = 1.00.

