All statistical analyses will be performed using Stata or R statistical software. The significance level will be set for 0.05 for all analyses and multiple testing adjustments will be performed by Bonferroni correction.

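### Plain Bonferroni is valid here, but Holm's step-down procedure would give the same family-wise error with at least as much power for stenting versus radiotherapy (optional, low-cost improvement)

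*Protocol article*

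**What the plan says.** The last paragraph of Statistical methods in the protocol article gives the general rule: "The significance level will be set for 0.05 for all analyses and multiple testing adjustments will be performed by Bonferroni correction". The Sample size section applies it to the primary analysis with an "alpha of 0.0167 (adjusting for 3 comparisons based on Bonferroni correction").

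The family is identified under Statistical methods: "Our primary analysis will examine pairwise comparisons of: stenting vs. radiotherapy with or without chemotherapy, stenting vs. chemotherapy", and, third, radiotherapy with or without chemotherapy against chemotherapy.

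The planning inputs are under Sample size. The expected numbers are "1102 study participants will be treated with esophageal stenting, 145 with chemotherapy, 464 with radiotherapy, 212 with concurrent chemoradiation". The assumed survival is "median OS following stenting is 36 weeks [10], radiotherapy with or without chemotherapy is 27 weeks [13, 19], and chemotherapy is 14 weeks". The stated powers at 0.0167 are "stenting vs. radiotherapy with or without chemotherapy, power = 0.99"; "stenting vs. chemotherapy, power = 1.00"; and "radiotherapy with or without chemotherapy vs. chemotherapy, power = 1.00".

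The sections agree with each other on the family and on the level. The article mentions no stepwise procedure.

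**The concern.** The plan expects two of its three primary hypotheses to be rejected almost with certainty. Plain Bonferroni makes no use of this: the third, stenting versus radiotherapy, stays at 0.0167 whatever happens to the other two. Holm's procedure passes the released error rate on. It compares the ordered p-values with 0.0167, 0.025 and 0.05 and stops at the first failure, and its family-wise error is still at most 0.05.

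Stenting versus radiotherapy has the smallest planned difference of the three, and the Discussion dwells on the trade-off between these two treatments. Its planned hazard ratio rests on medians from separate earlier sources, while the study will compare non-randomised groups with covariate adjustment. The adjusted hazard ratio could therefore lie closer to 1 than planned, and in that region the choice between 0.0167 and 0.05 costs power.

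**Working it through.** **Inputs from Sample size.** Stenting 1102; radiotherapy with or without chemotherapy 464 + 212 = 676; chemotherapy 145. Medians 36, 27 and 14 weeks. With exponential survival the hazard ratios are 27/36 = 0.75 (stenting vs radiotherapy), 14/36 = 0.39 (stenting vs chemotherapy) and 14/27 = 0.52 (radiotherapy vs chemotherapy).

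**Assumptions, not in the article.** Two-sided tests; the fraction of patients whose death is observed (85% unless stated otherwise); hazard ratios of 0.85, 0.87 and 0.90 as smaller effects than planned.

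**Formula (Schoenfeld).** z = |ln HR| × √(d·p·(1−p)) and power ≈ Φ(z − c). Here d is the number of deaths and p the share of patients in the first group. The critical value c is 2.394 at 0.0167 and 1.960 at 0.05.

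**1. The plan's own figures reproduce.** For stenting vs radiotherapy, p = 1102/1778 = 0.620. Power at 0.0167 is 0.9998 if all 1778 die and 0.998 with 80% deaths. With 14 months' accrual, 6 months' further follow-up and no loss it is 0.993. Exactly 0.99 corresponds to 1143 deaths. Both contrasts against chemotherapy give 1.00 with 80% or more deaths. The stated 0.99, 1.00 and 1.00 stand.

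**2. The level Holm applies to stenting vs radiotherapy.** Suppose both chemotherapy contrasts have p ≤ 0.0167.
- If stenting vs radiotherapy also has p ≤ 0.0167, both procedures reject it.
- If its p exceeds 0.0167, it is the largest of the three and Holm compares it with 0.05.

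Its effective threshold is then 0.05. If a chemotherapy contrast is not rejected, the level stays at 0.0167 or 0.025.

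**3. Power for stenting vs radiotherapy.** With 85% deaths, d = 0.85 × 1778 = 1511 and √(1511 × 0.620 × 0.380) = 18.87. The radiotherapy vs chemotherapy hazard ratio is kept as planned, so both chemotherapy contrasts are still rejected with power 1.00.

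| HR | z | Bonferroni (0.0167) | Holm (0.05 in effect) |
|---|---|---|---|
| 0.75 (planned) | 5.43 | 0.999 | 1.000 |
| 0.85 | 3.07 | 0.75 | 0.87 |
| 0.87 | 2.63 | 0.59 | 0.75 |
| 0.90 | 1.99 | 0.34 | 0.51 |

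For example, at 0.85: Φ(3.067 − 2.394) = Φ(0.673) = 0.75 and Φ(3.067 − 1.960) = Φ(1.107) = 0.87. Simulating the three correlated log-hazard contrasts (400,000 draws) gives the same values. With 70% deaths, HR 0.85 gives 0.65 and 0.80.

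**4. If the chemotherapy effects are weaker too.** Shrinking all three log hazard ratios in proportion changes Holm's power to 0.86 at HR 0.85, 0.74 at 0.87 and 0.46 at 0.90. Bonferroni is unchanged.

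**5. Error rates.** When stenting and radiotherapy are truly equal and chemotherapy differs as planned, stenting vs radiotherapy is falsely rejected in about 5.0% of draws under Holm and 1.7% under Bonferroni. When all three are equal, the family-wise error is the same for both, about 4.1%.

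**6. In events.** For 80% power the ratio is ((1.960 + 0.842)/(2.394 + 0.842))² = 0.75. A test at 0.05 needs 25% fewer deaths than one at 0.0167.

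**The case against.** The strongest reply is that nothing is wrong. Bonferroni is a valid choice, 0.05/3 is right, the sections agree, and at the plan's own inputs power is already 0.99 or more. All of that stands: at the planned hazard ratio the gain with 85% deaths is about 0.1 percentage point, and no sample size depends on it.

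Second, the hazard ratios of 0.85 to 0.90 are assumptions. Because 36/27 × 27/14 = 36/14, the first ratio cannot move with both chemotherapy ratios left as planned. This also stands. It lowers the gain mainly at HR 0.90 (to 0.46 rather than 0.51) and barely at 0.85.

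Third, Holm does not come with the simple simultaneous confidence intervals that match Bonferroni, and recruitment began in February 2019, so a prespecified threshold would be relaxed during accrual. Both are fair. The first is met by still reporting Bonferroni intervals, the second by fixing the change before outcomes are analysed.

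Two stronger readings are tempting, and the documents support neither. A reader might infer that Holm tests stenting versus radiotherapy at 0.05 outright; it does so only after both chemotherapy contrasts have been rejected. A reader might also infer that the planned overall log-rank test, followed by pairwise tests at 0.05, already forms a closed procedure. Statistical methods describes that test only as comparing treatments overall and lists six modalities, including esophagectomy and supportive care alone. A test across those groups could reject because of a group outside the primary family, so it would not protect the three pairwise tests.

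**Conclusion.** The point holds as an optional, inexpensive improvement. The plan uses plain Bonferroni; Holm controls the same 0.05 family-wise error without added assumptions and rejects everything that Bonferroni rejects.

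Under the planned medians the benefit is negligible. It becomes material only if the true stenting versus radiotherapy difference is smaller than planned: roughly 12 percentage points of power at a hazard ratio of 0.85, and 12 to 17 points at 0.90 depending on how far the chemotherapy effects shrink as well. These sizes rest on the stated group sizes, proportional hazards, two-sided tests and an assumed 85% of deaths observed. They should not be read as showing that the study is underpowered or that its multiplicity rule is faulty.

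**What to change.** In the last paragraph of Statistical methods, replace the Bonferroni correction by Holm's step-down procedure within each declared family, starting with the three primary overall survival contrasts, the only family that the article counts explicitly. Record the change before any outcome analysis.

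Under Sample size, keep 0.0167 as the first-step level and state that the powers given are lower bounds under the same planning inputs.

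The change needs no extra patients or data. The costs are a short amendment, the need to say which tests form each family, and less direct matching simultaneous intervals; Bonferroni-adjusted intervals can be reported beside the Holm decisions.
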